### Participant timeline

Enrolment begins when presumptive study participants gain brief written and verbal information about the IPS-ADAS trial from professionals within the AS (Fig. 1). Once inclusion and exclusion criteria are broadly met (pre-screening), interested persons are invited to partake in an information/dialogue meeting (group/individually) to understand eligibility and the meaning of participating in the trial more fully, before signing their written consent (30–45 min). Their written consent may also be handed in afterwards. In connection to enrolment, baseline data is contained (questionnaire battery, 30–50 min) after which allocation to one of the two interventions (IPS + TAU and TVR + TAU) is performed. Participants will attend the interventions for 12 months. The questionnaire battery is repeated at 6 (168 days), 12 (365 days) and 18 months after the randomisation date, with a 21-day window after the due date at the 6- and 12-month follow-up, and 28 days at 18 months.

**Fig. 1 Fig1:**
[figure not shown]
Trial Figure of the IPS-ADAS trial

### Sample size

The primary outcome is used to calculate the required sample size to detect a significant mean difference between the intervention groups at 18 months follow-up (employment rate, yes/no). No previous trial has been published within the field of AS, why the estimation is done against previous IPS trials. According to Marsden et al. [28], using a DELTA^2^ guidance based a meta-analysis from 2019 [18], 302 participants were deemed to be a sufficient sample size (95% CI). When departing in previous Swedish high-fidelity IPS trials, targeting persons with psychosis [20] and depression [22], power calculations (Fisher’s exact test) show the required sample size of 60 and 40 respectively to detect a power of 80% and alpha level at 0.05 (95% CI). One point of departure for aiming at a larger sample size than previous trials is that the dropout rate for persons in AS is assessed to be equivalent or even larger than for those with mental health problems, according to the attendance rates in similar interventions within AS in one of our trial contexts (City of Stockholm). A rate of ≥ 30% drop-out must therefore be considered. Another point of departure regards the criticality to detect statistical a mean difference for secondary outcomes (e.g. ordinal data) which according to a meta-study needs to increase in IPS trials, overall [78]. Lastly, the employment specialists typically have a caseload of a maximum of 20. But since their capacity to support persons with addiction is unknown, the number of maximum participants we estimate to be 15. In all, we intend to involve 9 employment specialists (Stockholm, *n* = 5; Södertälje, *n* = 3, Lund/Malmö, *n* = 3). As a suggestion, the ambition is to include a total of approx. 165 + 165 participants, a total of 330, Stockholm (*n* = 150) and Södertälje (*n* = 90) (East Middle Sweden) and Malmö/Lund (*n* = 90) (Southern Sweden). Distribution of the participants between the locations may be adjusted in accordance with recruitment rates at each site.

### Recruitment, allocation, and blinding

For each site, enrolment will last for about 18 months, from September 2023 to February 2025. Healthcare professionals from AS will assist to identify eligible participants by reviewing health records and approaching users and screening will last until the population of the target is reached for each site. Verbal information will further be advertised in waiting rooms and on social media of research- and user organisations targeting the group of interest. In connection with this initial recruitment phase, it will also be possible for presumptive users to self-register and pose their interest at a website whereupon they are referred to healthcare professionals for brief oral and written information about eligibility.

If criteria are met, presumptive users will be invited to partake in an information meeting (group or individually) at their site. The meeting will target the interventions as well as issues around the RCT design, randomisation, and ethical approval. The content and delivery of the information meetings will follow a premade protocol description and meetings will be held by a healthcare professional and researchers, a research administrator, and a user representative with lived experience of addiction and re-entering employment. Family and friends of presumptive participants may also partake for support. The aim is to provide democratic spaces to inform eligible users and openly discuss the project. Individual meetings may be held by a healthcare professional or a researcher. Any time after attending the meeting users may hand in their written consent. The duration of the recruitment will be approximately 1 year for each site respectively.

After completion of baseline assessment, participants will be randomly assigned to one of the two intervention arms (ratio 1:1) using randomly varying block sizes, using a randomisation schedule automatically generated in RedCap to assure allocation concealment, with no stratification. A randomization list (Excel file) will be kept separate and be administrated by a research administrator who will manage the allocation sequence, enrollment of participants, and assignment to interventions by sending a standardised letter about the IPS + TAU and TVR + TAU intervention respectively by mail, within a week.

The trial will be single- and assessor-blinded, i.e. researchers will have no knowledge of the identity or allocation of users. It will not be possible to mask the allocation status for those receiving or delivering the interventions. Participants will be informed not to reveal their allocation status to research assistants who will be blinded. Once data collection has been completed the independent research assistant will code the allocation status (As and Bs) to ensure blinding throughout analysis and conclusion of results.

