### Eligibility criteria and informed consent

Eligibility criteria concern having a working age of 18–65, willingness to work, being unemployed, participation in an IPS-ADAS trial information meeting, being diagnosed with addiction disorder (i.e. alcohol and/or drugs) as a primary diagnosis and in treatment at outpatient AS within the healthcare Region and/or related Municipality, and being financially supported by welfare system (i.e. the Municipality, Public Employment Service or Social Insurance Agency).

Exclusion criteria regard having a lack of interest to become employed and to participate in the IPS-ADAS trial, ongoing abstinence treatment, disability because of another main condition (e.g. serious mental illness, somatic illness), lack of ability to fully engage in IPS due to acute homelessness, being engaged in a lengthy legal process, occupied with plans of suicide, or having had recent attempts (< 3 months).

Eligibility criteria for the sites will concern being an AS provider within the publicly financed healthcare of Region Stockholm and Region Skåne and/or City of Stockholm, Municipality of Södertälje, and Municipality of Lund/Malmö. The trial may be extended to other sites. AS in Sweden are typically divided between Regions and Municipalities and new governmental directives for coproduction and person-centeredness of services are policy [15].

The Employment Specialist is the key professional of the IPS intervention and will have formal IPS training, work experience of IPS, and a position within above stated regions or municipalities.

The AS provider will take informed consent. Initially the professional will provide verbal and written information about the IPS-ADAS trial, including the possible benefits, risks, and alternative interventions. If interested, presumptive participants will be scheduled for an obligatory IPS-ADAS information meeting in a group format or individually. A research administrator, a professional from AS, and a user representative with experienced knowledge of addiction and returning to work will aid presumptive participants to understand the trial more fully, criteria, confidentiality, and the voluntary nature of participation. If criteria are met, the informed consent form may be signed, available on request from the corresponding author.

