The Hospital Anxiety and Depression Scale (HADS) has 14 items and assists to measure mental health in terms of differences between intervention arms regarding anxiety (7 items) and depression (7 items) [67], also among persons with substance abuse [68]. It is rated on a 4-point scale (0–3 range), and anxiety and depression are scored separately (0 to 21). A higher score indicates a greater level of anxiety and depression, and cut-off scores are available [69]. HADS is used in general medical settings, including occupational health, with sound psychometric properties [70].

The Assessment Severity Index (ASI) is widely used to address the severity of substance use, health and social problems and the need of treatment. ASI holds 7 key domains: medical status, employment and support, drug and alcohol use, legal status, social and psychiatric status [71, 72], and has sound psychometric properties [73]. In the present IPS-ADAS trial, the ASI interview questions are replied online (RedCap), with support from the research administrator if needed. Variables relevant to sociodemographic characteristics, substance abuse and care and support are particularly of interest for the present study (i.e. age, gender/gender identity, ethnicity, civil status, diagnosis, substance use, housing situation, income, benefit type, sick-leave status, education and employment status, treatment, care, and support). A composite score may be summarised for ASI, but the rationale for using the ASI questions in the trial is to benefit from the context-specific index developed for the target group within AS.

Quality of life (QoL) outcomes are assessed by the EuroQol 5 Dimension (EQ-5D) [74] and the Manchester Short Assessment of Quality of Life (MANSA) instrument (see below) [75]. The EQ-5D is used to study the effectiveness of perceived QoL dimensions. It comprises 5 health-related quality of life dimensions, mobility, self-care, usual activities, pain/discomfort, and anxiety/depression with three gravity levels (no problem, moderate problem, and extreme problem), and a visual analogue scale on global QoL (1–100) [74]. An economic evaluation is also available, i.e. the scoring of dimensions helps to quantify 243 health states that can be converted to an index utility score and further translated according to country-specific tariffs which value may be considered as the quality-adjusted life-years (QALY). EQ-5D is well known to assess health interventions, also IPS [24].

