Baseline and follow-up data will be collected by means of questionnaires online via RedCap (Research Electronic Data Capture) [58] and will take about 30–45 min to complete. Data collection on clinical, social, and demographic characteristics, will be obtained by the ASI, while secondary outcomes on health, quality of life and well-being by psychometrically sound self-reported instruments tested within the field and assist to increase the external validity of the trial [21–24, 28, 29]. Instruments are further detailed in the Outcomes section. Data collection will be administered via Lund University and the online survey platform for clinical trials (REDCap) [58] at − *t*^1^, *t*^1^–*t*^4^ (see Table 1) and include all participants unless they withdraw. They will receive an e-mail with a link to the survey and respond to the questions online, or if they prefer a pen-and-paper format. They may also ask for personal assistance by the research assistant or peer support, both having received 1-day education about concepts, psychometry, and interview training by the trial management group. Either option, responses are registered in the RedCap system (Research Electronic Data Capture) hosted by Lund University. Response preferences are listed by the administrator who according to a follow-up schedule may remind or prompt participants via their personal choice of contact, to fulfil questionnaires and follow-ups. All data will be stored in LUSEC which is an all-inclusive “virtual desk” for storing, managing, and analysing personal and sensitive data that requires high security in compliance with legislation, for example, the EU’s General Data Protection Regulation (GDPR). The platform has a storage solution with encryption of data, a secure user environment with a two-step log-in system using two applications, and a secure file transfer software. Physical material will be stored in secured cupboards in locked fire-safe facilities.

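### The role that keeps the randomisation list also manages enrolment and assignment, which undermines the claimed concealment if the list shows upcoming allocations; the same role may also help with ASI answers

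*Protocol article*

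**What the plan says.** In the protocol article, the section Recruitment, allocation, and blinding describes 1:1 assignment in randomly varying blocks after baseline, "using a randomisation schedule automatically generated in RedCap to assure allocation concealment, with no stratification". The next sentence adds a second object, a randomisation list in Excel that is held apart and "administrated by a research administrator who will manage the allocation sequence, enrollment of participants, and assignment to interventions"; the assignment is made by posting a letter.

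Under Eligibility criteria and informed consent, the people who help candidates understand the trial at the obligatory information meeting are "A research administrator, a professional from AS, and a user representative". The Addiction Services provider takes consent.

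Under Secondary outcome, the ASI is answered online "with support from the research administrator if needed". Data collection and management describes help differently: participants may "ask for personal assistance by the research assistant or peer support". That section also has the administrator keep a list of response preferences and remind or prompt participants on a follow-up schedule. On blinding, participants are told "not to reveal their allocation status to research assistants who will be blinded".

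**The concern.** Concealment requires that nobody involved in bringing a person into the trial can know that person's arm before entry is settled. The text assigns custody of the sequence, enrolment and assignment to one role, and puts that role title in the meeting that precedes consent. If the list can be read ahead, entry can be encouraged, discouraged or delayed according to the next arm. A register outcome gives no protection here. It guards against biased recording of employment, not against arms that differ in job readiness from the start, and covariate adjustment removes only the differences that were measured.

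The second issue concerns follow-up. The role that mails the allocation letters knows the arms. If it helps with ASI answers or chases responses, the answers and the response rate can both be influenced by someone who is not blinded. The ASI supplies substance use, care and support data, and the self-reported employment status against which the register is validated.

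**Working it through.** No figure in the document bears on this point, so the check is a comparison of the text.

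1. **Who can see the sequence.** The schedule is generated in REDCap, but there is also an Excel list run by a research administrator. The article says the list is kept separate, without saying from what, and does not say whether it holds future allocations or only past ones. Managing the sequence suggests the former but does not settle it.

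2. **What follows under each reading.**
   - If the file holds upcoming allocations, randomly varying blocks give no protection, because the next arm is read and not guessed.
   - If it is a log of allocations already made, the varying blocks limit prediction. Some inference near the end of a block may remain; the block sizes are not given.

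3. **Whether the role has a route to influence entry.**
   - Recruitment, allocation, and blinding: Addiction Services staff identify and approach candidates, but enrolment is listed among the administrator's duties.
   - The same section and Eligibility criteria and informed consent: a research administrator is named for the information meetings. Individual meetings may instead be held by a healthcare professional or a researcher.
   - Consent may be handed in at any time after the meeting, and allocation follows completed baseline. The date of entry is therefore flexible.

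   The route exists on paper, but the administrator is not described as deciding eligibility or taking consent.

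4. **Who helps with follow-up answers.**
   - Secondary outcome (ASI): the research administrator, if needed.
   - Data collection and management: the research assistant or peer support; the administrator reminds and prompts.
   - Recruitment, allocation, and blinding: research assistants are blinded; the administrator sends the letters and is nowhere said to be blinded.

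   The first statement does not fit with the other two.

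5. **Which outcomes are exposed.** The primary outcome comes from Statistics Sweden through the LISA register (Primary outcome), and so do the secondary vocational outcomes (Secondary outcome). Neither passes through a helper. What is exposed is follow-up ASI data given with the administrator's help, and response to questionnaires after prompting. ASI employment status serves only to validate the register, by an independent researcher who also uses the employment specialists' logbooks. ASI help at baseline comes before allocation and cannot unblind, provided the sequence is hidden from the helper.

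**The case against.** The strongest reply is that the administrator is not the gatekeeper. Addiction Services professionals pre-screen, the provider takes consent, group meetings have several hosts and follow a set description, and randomisation waits for baseline. Enrolment in the list of duties may mean no more than registering people and posting letters, and the Excel file may be only a log. This stands as a limit: it makes the exposure conditional and narrower. It does not remove it, because the text as written joins the sequence and enrolment in one role and does not say what the file shows.

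Three stronger readings are tempting, and the document does not support them.

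- A reader might infer that one individual holds the list, attends the meetings and helps with the ASI. The text shows a shared role title only, and the Monitoring section speaks of research administrators in the plural.
- A reader might infer that assessor blinding fails as a whole. Help from blinded research assistants is planned, the administrator's help with answers is stated for the ASI alone and only when needed, and the primary outcome involves no assessor. Participants are openly unmasked in any case.
- A reader might want a figure for the bias in the employment difference. That needs the share of entrants whose entry could be influenced, and how far their chance of a job differs from that of others. The document gives neither, nor any expected employment rate, so a figure would rest wholly on invented inputs.

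**Conclusion.** The point holds in two parts of unequal weight.

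The first is concealment. The protocol asserts it and then states an arrangement that undermines it, if the list shows upcoming allocations. The consequence would be selection into the arms, which affects the primary comparison however employment is recorded. The direction and size are unknown. The conclusion assumes that enrolment carries some influence over who enters or when, which the text allows but does not spell out.

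The second is an internal conflict over who assists and prompts participants at follow-up. It is confined to assisted self-reported ASI data (substance use, care use and the employment self-report used for validation) and to response rates. It leaves the register-based outcomes untouched.

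**What to change.** - Keep the sequence only inside the REDCap randomisation module, hidden from anyone who takes part in information meetings or enrolment. Release each allocation only after consent and baseline are complete.
- State what the Excel file contains. Limit it to a log of allocations already made, held by someone with no part in enrolment.
- Bar staff who know allocation from follow-up questionnaire support, and give reminders and prompts to blinded staff or an automated message. REDCap e-mail reminders are already planned.
- Reconcile the ASI paragraph under Secondary outcome with Data collection and management and with the blinding paragraph, and say whether peer supporters know allocation.
- Recruitment was planned to end on 28 February 2025 and data collection on 30 June 2026. If recruitment has closed, the trial report should say what the list showed and who could open it; the follow-up changes apply for as long as data are still being collected.

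The cost is a reassignment of tasks and REDCap user rights among existing roles. No change to sample size, outcomes or analysis is needed.

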### Data collection and management

Researchers will retrieve anonymised primary and secondary vocational, income and benefit data from the LISA database in which data from the labour market, social and educational sector is integrated and updated annually, focusing on the individual as the primary object. Data will be retrieved by Statistics Sweden and the procedure is that the research assistant will submit personal security number data with a variable order to Statistics Sweden which they co-run and deliver back to the researchers pseudonymised. In addition, vocational data will be registered by the participants in connection to RedCap data collection (ASI).

Baseline and follow-up data will be collected by means of questionnaires online via RedCap (Research Electronic Data Capture) [58] and will take about 30–45 min to complete. Data collection on clinical, social, and demographic characteristics, will be obtained by the ASI, while secondary outcomes on health, quality of life and well-being by psychometrically sound self-reported instruments tested within the field and assist to increase the external validity of the trial [21–24, 28, 29]. Instruments are further detailed in the Outcomes section. Data collection will be administered via Lund University and the online survey platform for clinical trials (REDCap) [58] at − *t*^1^, *t*^1^–*t*^4^ (see Table 1) and include all participants unless they withdraw. They will receive an e-mail with a link to the survey and respond to the questions online, or if they prefer a pen-and-paper format. They may also ask for personal assistance by the research assistant or peer support, both having received 1-day education about concepts, psychometry, and interview training by the trial management group. Either option, responses are registered in the RedCap system (Research Electronic Data Capture) hosted by Lund University. Response preferences are listed by the administrator who according to a follow-up schedule may remind or prompt participants via their personal choice of contact, to fulfil questionnaires and follow-ups. All data will be stored in LUSEC which is an all-inclusive “virtual desk” for storing, managing, and analysing personal and sensitive data that requires high security in compliance with legislation, for example, the EU’s General Data Protection Regulation (GDPR). The platform has a storage solution with encryption of data, a secure user environment with a two-step log-in system using two applications, and a secure file transfer software. Physical material will be stored in secured cupboards in locked fire-safe facilities.

